### 10.1 Primary study parameter(s)

#### *Insulin sensitivity*

Insulin sensitivity will be measured by means of a 6-hour hyperinsulinemic euglycemic clamp. Insulin sensitivity will be presented quantitatively for:

- Whole body insulin sensitivity (primarily muscle): GIR ( $\mu\text{mol/kg/min}$ ).
- Peripheral insulin sensitivity: Rd ( $\mu\text{mol/kg/min}$ ).

#### *Metabolic flexibility*

Metabolic flexibility will be computed as the difference in respiratory quotient (RQ) between the basal and insulin stimulate state during the 6-hour hyperinsulinemic euglycemic clamp. The RQ will be computed via  $RQ = \text{vCO}_2/\text{vO}_2$  in which CO2 and O2 are measured via the indirect calorimetry.

To find out whether the time course of insulin sensitivity (whole body glucose infusion rate or RD) is different in the three different treatments (LIPID+Carnitine (treatment A), LIPID+Placebo (treatment B) and Saline+Placebo (treatment C)) a two-way ANOVA for repeated measures is used. Therefore, the dependent variable is “insulin sensitivity”, whilst the two factors are the “conditions” (i.e., three groups: “treatment A”: the Lipid+carnitine, “treatment B”: the Lipid+Placebo, “treatment C”: the Saline+Placebo) and “time”. Post-hoc tests will determine where the significant differences are. The metabolic flexibility ( $\Delta$  RER between basal and insulin stimulated state) will be determined by comparing metabolic flexibility between the conditions with a one-way ANOVA.

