## 2. OBJECTIVES

Primary Objective:

- To investigate whether L-carnitine infusion may rescue lipid-induced insulin resistance
- To investigate whether L-carnitine infusion is improving metabolic flexibility in the state of lipid-induced insulin resistance.

Secondary Objective:

- To examine the molecular pathways of carnitine and acetylcarnitine responsible for muscle insulin sensitivity

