**Visit 4/5/6 (hyperinsulinemic euglycemic clamp):** During visit 4,5, and 6 a 6-hour hyperinsulinemic euglycemic clamp measurement will be carried out. During each visit (visit 4,5,6) a different trial arm will be tested (trial arm 1: LIPID + CAR, trial arm 2: LIPID + PLAC, trial arm 3: SALINE + PLAC). Subjects will be randomly allocated to the different trials arms. Subjects report to the university after an overnight fast (8PM) at 7AM. We will place an intravenous cannula into the forearm, take a blood sample and begin infusing the glucose tracer (this is part of the preperaring steps for the clamp). Next, we will take the first muscle biopsy. Hereafter, we will continue with a 30 minute indirect calorimetry measurement and the 6-hour hyperinsulinemic euglycemic clamp as described in chapter 8.3. At the end of the clamp we will take a second muscle biopsy of the m. vastus lateralis. The test ends and the subject will receive lunch. The subject will be discharged at 5PM provided blood glucose levels are stable. Three days prior to visit 4,5 and 6, the subjects will be asked to withstand from alcohol, refrain from strenuous physical activity and adhere to their normal eating pattern. During these three days, subjects fill out a food diary to monitor if food intake is equal before the test periods (Appendix F2). Furthermore, subjects will be asked to consume a standardized meal the evening before the 6-hour hyperinsulinemic euglycemic test days (visit 4,5,6), followed by an overnight fast (from 8PM). The meal will be a ready to eat meal "macaroni bolognaise" bought in the local supermarket. Visit 4,5 and 6 will be separated by at least two weeks.

An overview of the entire study is provided in figure 5:

[figure not shown]

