### 4.4 Sample size calculation

The improvement in insulin sensitivity, determined by a clamp (whole body glucose utilization) combined with carnitine infusion is assumed to be around 0.5 mg/kg/min  $\pm$  0.68 mg/kg/min [7, 11-13], therefore  $\mu=0.5$  mg/kg/min. The variation in the individual improvement upon carnitine infusion is estimated to be 0.68 mg/kg/min ( $\sigma=0.68$ ). Using the following online power calculator for cross-over trials

([http://hedwig.mgh.harvard.edu/sample\\_size/js/js\\_crossover\\_quant.html](http://hedwig.mgh.harvard.edu/sample_size/js/js_crossover_quant.html)), sample size was calculated. To reach a power ( $1-\beta$ ) of 80% and a significance level ( $\alpha$ ) of 0.05 (one-sided) a minimal sample size of N=13 was calculated according to the online power calculator. One-sided testing is adequate as the hypothesis will be tested that carnitine *improves* insulin sensitivity.

Considering a drop-out of 20% ( $(13/100)*20 = 3$  subjects) we will need to include 3 extra subjects in the study, so a total inclusion of 16 subjects. Taking into account exclusion after screening in 30% of the cases, we will need to screen 21 subjects.

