## 5. TREATMENT OF SUBJECTS

### 5.1 Investigational product/treatment

This is a cross-over randomized trial, in which each subject will participate in three trial arms (visit 4,5,6). Thus, each subject will act as its own control. In all three trial arms insulin sensitivity will be measured during a 6-hour hyperinsulinemic euglycemic clamp and two muscle biopsies will be obtained. Subjects will begin with either of the trial arms at random order. To investigate if L-carnitine infusion may rescue lipid-induced insulin resistance, we will induce insulin resistance by lipid infusion (arm 1 & 2) and test whether co-infusion of L-carnitine can alleviate insulin sensitivity. Trial arm 1 (LIPID + CAR) is therefore the intervention arm with actual co-infusion of L-carnitine and trial arm 2 will serve as a control arm due to substitution of L-carnitine administration by infusing saline. L-carnitine is therefore the investigational product in this study.

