#### *Metabolic compounds*

Time effects of metabolites in plasma (i.e. glucose, free fatty acids, triglycerides, cholesterol, insulin) will be presented quantitatively and analyzed using a two way ANOVA repeated measures analysis for analyzing data over time.

*Skeletal muscle mRNA and protein levels at baseline and during insulin stimulation*

Skeletal muscles parameters of the carnitine mechanism (such as CrAT activity and acetylcarnitine profiles) as well as lipid intermediates will be analyzed comparing pre and post clamp values using a paired sampled T-test. Differences between intervention arms (LIPID+CAR, LIPID+PLAC, SALINE+PLAC) will be analyzed with a one way ANOVA for repeated measured with post-hoc analysis if data allow to do so.

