**Appendix 1A: Randomisation intervention arms**

| Randomisation
(Set=subject) | Visit 4 | Visit 5 | Visit 6 |
|--------------------------------|---------|---------|---------|
| Set 1                          | 3       | 2       | 1       |
| Set 2                          | 2       | 3       | 1       |
| Set 3                          | 1       | 3       | 2       |
| Set 4                          | 2       | 1       | 3       |
| Set 5                          | 1       | 2       | 3       |
| Set 6                          | 3       | 1       | 2       |
| Set 7                          | 1       | 2       | 3       |
| Set 8                          | 2       | 1       | 3       |
| Set 9                          | 2       | 3       | 1       |
| Set 10                         | 3       | 2       | 1       |
| Set 11                         | 3       | 1       | 2       |
| Set 12                         | 1       | 3       | 2       |
| Set 13                         | 2       | 1       | 3       |

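### Section 10.1 tests metabolic flexibility with a plain one-way ANOVA although every subject has all three conditions; taken literally, the test is conservative and loses power

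*Protocol*

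**What the plan says.** Metabolic flexibility serves one of the two primary objectives in section 2 ("To investigate whether L-carnitine infusion is improving metabolic flexibility in the state of lipid-induced insulin resistance") and is listed as a main endpoint in section 8.1.1. Each subject undergoes LIPID+CAR, LIPID+PLAC and SALINE+PLAC over visits 4 to 6. Section 5.1 adds that "Subjects will begin with either of the trial arms at random order".

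The protocol names three analyses for comparing conditions:

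- GIR and Rd (section 10.1): "a two-way ANOVA for repeated measures is used", with condition and time as the two factors. Time is the time course within a clamp, not the visit.
- Delta RER (section 10.1, same paragraph): "determined by comparing metabolic flexibility between the conditions with a one-way ANOVA".
- Muscle parameters (section 10.2): differences between arms "will be analyzed with a one way ANOVA for repeated measured with post-hoc analysis if data allow to do so".

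None of these includes a term for visit.

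**The concern.** A one-way ANOVA across three conditions treats the 39 values (13 subjects times 3) as independent. In this trial they are 13 sets of three correlated values. Stable differences between subjects cancel from a comparison of condition means, because every subject contributes to every mean. They do not cancel from the one-way error term. The statistic is therefore divided by too large an error, and the gain in precision that justifies a crossover is lost for this endpoint. At stake is a missed effect on a primary objective, in a small study that takes six biopsies per subject.

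A smaller matter is the visit term. Order is randomised over three visits, and any drift from visit to visit would enter the error against which condition is tested.

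**Working it through.** **Inputs.** From section 4.4: effect 0.50 mg/kg/min, SD of the individual difference 0.68, one-sided alpha 0.05, N = 13. From Appendix 1A: the 13 condition orders, coded as in section 8.2. The protocol gives no effect, SD or intraclass correlation (ICC) for delta RER. The standardised effect 0.50/0.68 is borrowed from GIR, and ICCs of 0.3, 0.5 and 0.7 are assumed.

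**The plan's own figure.** A paired t-test, one-sided 0.05, with noncentrality 0.50/0.68 × √13 and 12 df, has power 80.3%. N = 13 reproduces.

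**Error term for delta RER.** The within-subject variance is σw² = 0.68²/2 = 0.2312. With subject in the model, the error estimates σw² on 24 df. In the one-way ANOVA it estimates σw² plus the between-subject variance, which equals σw²/(1 − ICC), on 36 df. The inflation is 1/0.7 = 1.43, 1/0.5 = 2.00 and 1/0.3 = 3.33 at ICC 0.3, 0.5 and 0.7.

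**Overall F test** (5% level; one condition shifted by 0.50, the other two equal). The noncentrality with subject in the model is 13 × (0.50² × 2/3)/0.2312 = 9.37. On 2 and 24 df this gives power 73.2%. The one-way results for ICC above 0 are simulated (200,000 runs); the power at ICC 0 is exact.

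| ICC | Power, one-way | Power, subject in model | Type I error, one-way |
|---|---|---|---|
| 0 | 75.1% | 73.2% | 5.0% |
| 0.3 | 57.5% | 73.2% | 1.7% |
| 0.5 | 37.8% | 73.2% | 0.5% |
| 0.7 | 13.2% | 73.2% | 0.1% |

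**One-sided pairwise contrast**, LIPID+CAR against LIPID+PLAC, using the one-way pooled error: power is about 74%, 61% and 36% at ICC 0.3, 0.5 and 0.7, against 82.4% with subject in the model. At ICC 0 it is 83.0% against 82.4%.

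**Cost of the subject term.** The error df fall from 36 to 24. In the worst case, ICC 0, the F test loses 75.1 − 73.2 = 1.9 points.

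**Visit term.** In Appendix 1A, the visit number of LIPID+CAR minus that of LIPID+PLAC for sets 1 to 13 is −1, 1, −1, 2, 1, −2, 1, 2, 1, −1, −2, −1, 2. The sum is 2 and the mean is 2/13 = 0.154 visits. Sets 1 to 12 sum to 0.

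Adding visit to a subject-plus-condition model on this list changes the contrast variance from 0.15385 σw² (= 2/13) to 0.15476 σw², a ratio of 1.006. The error df go from 24 to 22. Power for the pairwise contrast goes from 82.4% to 82.0% one-sided, or from 72.0% to 71.4% two-sided.

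**The case against.** **It may be shorthand.** The protocol says that each subject acts as its own control, and the preceding sentences of section 10.1 use repeated measures. The author may have meant the repeated-measures form for delta RER as well. That is possible and cannot be excluded. Against it, the same paragraph writes out repeated measures for GIR and Rd, and section 10.2 writes it out for a one-way comparison. The protocol draws the distinction elsewhere and leaves it out here.

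**The power figures are not this endpoint's own.** This stands. Effect, SD and ICC for delta RER are not given, so the figures illustrate the direction and possible size of the loss. The F test is the ANOVA as written. The one-sided contrast follows the sidedness in section 4.4, which section 10 does not repeat.

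**The visit term is a matter for the statistical analysis plan, and no harm is shown.** Largely right. The list is close to balanced. An assumed drift of 0.1 mg/kg/min per visit would shift the carnitine contrast by only 0.154 × 0.1 = 0.015. Section 4.4 plans for drop-out ("so a total inclusion of 16 subjects"), so the final balance may differ from the 13 listed sets, but nothing indicates a serious imbalance. A reader might infer that leaving visit out biases the carnitine comparison. The documents do not support that.

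**Carry-over.** A reader might also infer carry-over from the 139-hour half-life of carnitine release from muscle (section 12.1 f) together with the spacing rule ("Visit 4,5 and 6 will be separated by at least two weeks"). Neither the size of any retained increment nor its effect on GIR or RER is given, so no such conclusion can be drawn.

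**Conclusion.** The point holds for delta RER. As written, the test for a main endpoint ignores that the same subjects supply all three conditions. With positive within-subject correlation the result is a conservative test with less power, not an excess of false positives. How much is lost depends on the ICC: nothing at 0, and from 73% to about 58%, 38% or 13% for the overall F test at 0.3, 0.5 or 0.7. These figures assume the borrowed standardised effect, 13 complete subjects, and one condition differing from two equal ones.

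The absent visit term is real but minor. Adding it is a nearly free precaution, not the repair of an error. The whole finding is a low-severity change of wording.

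**What to change.** In section 10.1, replace the one-way ANOVA for metabolic flexibility with a repeated-measures ANOVA or a mixed model with random subject and fixed condition. With complete subjects the two give the same test of condition. If repeated measures was intended all along, the edit only states it.

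As an optional safeguard, add visit (4, 5, 6) as a fixed effect in the models for delta RER, GIR and Rd. Keep clamp time and condition-by-time for GIR and Rd.

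Cost: one paragraph of text, with no new subjects, visits or samples. For delta RER the error df go from 36 to 24 with subject, and to 22 with visit as well, so 14 in all. For a model that already contains subject, visit alone takes 2 df and adds 0.6% to the contrast variance, or 0.4 points of one-sided power.

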## 8. METHODS

### 8.1 Study parameters/endpoints

#### 8.1.1 Main study parameter/endpoint

6-hour hyperinsulinemic euglycemic clamp combined with tracer kinetics and indirect calorimetry:

- Whole body insulin sensitivity measured as GIR in  $\mu\text{mol/kg/min}$  during the stable period of the insulin phase of the clamp.
- Peripheral insulin sensitivity measured as  $R_d$  in  $\mu\text{mol/kg/min}$ .
- Metabolic flexibility (delta RER between basal and insulin stimulated state).

The hyperinsulinemic euglycemic clamp technique is considered the gold standard for assessing insulin sensitivity and metabolic flexibility [15].

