## 10. STATISTICAL ANALYSIS

For all study parameters data will be reported as minimum, maximum, mean  $\pm$  SD and/or  $\pm$  SEM. Statistical analysis will be performed using the statistical computer program SPSS. The Kolmogorov-Smirnov normality test will be performed to evaluate normality distribution. Pearson correlation coefficients will be computed to correlate parameter values. Differences will be considered significant when  $p < 0.05$ .

Missing values will not be replaced. If a missing value occurs for a specific parameter, the subject in question will not contribute to the analysis of that parameter.

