### **10.4 Interim analysis (if applicable)**

An interim analysis will be performed after 3 subjects have completely performed the entire study in order to confirm that the carnitine infusion model upon lipid induced insulin resistance works. It is known that type 2 diabetic patients are characterized by insulin resistance and metabolic inflexibility and that these characteristics are absent in young lean healthy subjects. Infusion of lipids in these young lean healthy subjects results in insulin resistance and decreased metabolic flexibility as in type 2 diabetic patients. This is characterized by a decrease in glucose infusion rate, glucose oxidation and increased fat oxidation rate during the clamp. Carnitine is suggested to rescue metabolic inflexibility and insulin resistance which would result in higher glucose infusion rates, glucose oxidation and decreased fat oxidation upon lipid infusion. To assure that carnitine indeed reaches the muscle we will check whether we see the expected patterns in substrate oxidation with or without addition of carnitine upon lipid infusion, and thus the model used in this study is adequate to answer our research question, we are performing an interim analysis after 3 subjects have completely performed the entire study (all three clamps). During the interim analysis, no new subjects will perform any test days before the results of the interim analysis is known. In case no changes occur in glucose infusion rate or substrate oxidation, the study will not be continued, as in that case, the study set-up is not suited to investigate the molecular mechanisms underlying the beneficial effects of carnitine.

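### The one test stated for metabolic flexibility, a three-condition ANOVA, does not test the carnitine objective; the within-subject LIPID+CAR minus LIPID+PLAC contrast should be named instead

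*Protocol*

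**What the plan says.** Section 2 lists as a primary objective "To investigate whether L-carnitine infusion is improving metabolic flexibility in the state of lipid-induced insulin resistance". Section 8.1.1 places delta RER, basal to insulin-stimulated, among the main study parameters beside GIR and Rd.

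Section 10.1 deals first with GIR and Rd. It names the three treatments, specifies a two-way repeated-measures ANOVA of condition and time, and adds: "Post-hoc tests will determine where the significant differences are". The next sentence, on delta RER, says that it "will be determined by comparing metabolic flexibility between the conditions with a one-way ANOVA". No pairwise comparison is attached to that sentence.

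Section 10.2 says that differences between arms in the muscle parameters "will be analyzed with a one way ANOVA for repeated measured with post-hoc analysis if data allow to do so". The only other analysis that names metabolic flexibility is a correlation with acetylcarnitine, also in Section 10.2.

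Section 10.4 describes the model: "Infusion of lipids in these young lean healthy subjects results in insulin resistance and decreased metabolic flexibility as in type 2 diabetic patients".

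**The concern.** The objective is about carnitine against a fixed lipid background, so its null is that LIPID+CAR and LIPID+PLAC have the same mean delta RER. The stated test has a wider null: LIPID+CAR, LIPID+PLAC and SALINE+PLAC all share one mean. By the protocol's own account of the model, the saline arm differs from the lipid arms. The wider null is then false even if carnitine does nothing.

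A significant F would show that the three conditions are not all alike, which the protocol already expects. It would not say whether carnitine contributed. A primary objective is thus left with a between-condition test that cannot answer it.

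This is separate from the question of whether the one-way ANOVA respects the crossover pairing. Changing to a repeated-measures omnibus test keeps the same three-condition null and detects the lipid effect more often.

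**Working it through.** **Inputs.** From Section 4.4: N=13, planned carnitine effect on clamp glucose utilisation 0.5 mg/kg/min, SD of the individual improvement 0.68, alpha 0.05 one-sided, power 80%. From Section 10: significance at 0.05, sidedness not stated. From Section 10.1: three conditions. The protocol gives neither a size nor an SD for the lipid effect on delta RER, so that effect is assumed at 0.5 to 1.5 total SDs, with within-subject correlation (rho) of 0.3 to 0.7.

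**The plan's own figure.** For a paired comparison, the normal approximation gives n = ((1.645 + 0.842) × 0.68 / 0.5)² = 11.4, so 12. With the noncentral t, n=12 gives 77.1% and n=13 gives 80.3% power, one-sided. N=13 reproduces, and it rests on the paired carnitine difference. Two-sided, n=13 gives 68.3%.

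**Omnibus test with no carnitine effect.** Means are set to (0, 0, L), where L is the lipid effect. The ordinary one-way F has 2 and 36 df. It was simulated on correlated data because it ignores the pairing. The repeated-measures F has 2 and 24 df. Results are from 20,000 to 40,000 simulated trials per setting; repeat runs move an entry by up to about one percentage point.

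| Lipid effect (total SD) | One-way ANOVA, as written | Repeated-measures omnibus | Paired LIPID+CAR vs LIPID+PLAC |
|---|---|---|---|
| 0.5 | 8–17% | 30–61% | 5% |
| 0.75 | 37–42% | 59–93% | 5% |
| 1.0 | 73–76% | 85–100% | 5% |
| 1.5 | 99% | about 100% | 5% |

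Ranges span rho 0.3 to 0.7. The one-way ANOVA passes 50% rejection between about 0.80 and 0.85 SD.

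The repeated-measures column can be checked by formula. Write dz for L divided by the SD of the within-subject difference. The noncentrality is 13 × (4/3) × dz². At dz = 1 this is 17.3, which gives 95% rejection. Rejection passes 50% at dz = 0.57.

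**If the post-hoc sentence covers delta RER.** With no carnitine effect and the same lipid range, the omnibus test followed by a LIPID+CAR vs LIPID+PLAC comparison declares a carnitine effect in about 0.1–2% of trials (one-way, unadjusted pairwise) or about 4–5% (repeated measures, paired t). There is no inflation.

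For power, take the standardised effect planned for GIR, 0.5/0.68 = 0.735 SDs of the difference. For delta RER this is an assumption. The paired statistic is centred near 0.735 × √13 = 2.65. An unpaired comparison divides by the total SD, so it is centred near 0.735 × √(13 × (1 − rho)):

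- rho 0.3: 2.22
- rho 0.5: 1.87
- rho 0.7: 1.45

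Tukey's critical value on this scale is about 2.44. Power is about 41% at rho 0.3, falling to 8% at rho 0.7. Unadjusted pairwise tests have about 59% falling to 19%. The paired contrast has 68% two-sided or 80% one-sided at any rho.

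**The case against.** **No rule says a significant F counts for carnitine.** This stands. Section 10.1 only compares the conditions, and rejecting three equal means because lipid lowers delta RER is a correct rejection of that null. A reader might infer that the plan commits to a false carnitine claim, but the documents do not support that. What remains is that the stated test does not address the objective.

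**The roles of the arms are described elsewhere.** The Summary and Section 5.1 make LIPID+PLAC the control for carnitine, and the Summary and Section 3 make SALINE+PLAC the control for lipid. Section 10.4 looks at patterns with and without carnitine during lipid infusion. The authors clearly have the right comparison in mind, but Section 10.1 does not carry it into the test for delta RER.

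**The post-hoc sentence may apply.** It is general, stands directly before the delta RER sentence and sits under the same subheading. Its placement ties it more naturally to the two-way ANOVA, and Section 10.2 shows post-hoc analysis being named where it is meant. The wider reading is still possible, and under it the false-positive concern disappears. The power problem then takes its place.

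**The SAP may settle it.** Naming follow-up comparisons is often left to a SAP, and none is shown. The point here, however, is a test that the protocol does state and that does not match a primary objective.

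**Weight.** The Summary names whole-body insulin sensitivity as the primary endpoint, and the trial is sized on it. Neither the sample size nor the GIR analysis is touched.

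**Conclusion.** The point holds as a mismatch between a stated test and a primary objective. Given the protocol's premise that lipid lowers metabolic flexibility, the three-condition null is expected to fail without any help from carnitine, and a significant F is uninformative about carnitine. That conclusion needs only a non-zero lipid effect.

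A reader might go further and infer that the ANOVA will usually be significant when carnitine does nothing. The documents do not support this, because no lipid effect or SD for delta RER is given. For the test as written it is true only above roughly 0.8–0.85 total SD; at 0.5 SD the rate is 8–17%.

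On the lenient reading of the post-hoc sentence there is no excess of false carnitine findings. The cost is then power: about 8–41% with Tukey against 68% (two-sided) or 80% (one-sided) for the paired contrast. These figures assume the GIR standardised effect carries over to delta RER and that rho lies between 0.3 and 0.7. On either reading the paired contrast is the better test. The change is worth making before analysis.

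**What to change.** In Section 10.1, replace the delta RER sentence with wording to this effect:

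*The effect of carnitine on metabolic flexibility is tested by the within-subject contrast LIPID+CAR minus LIPID+PLAC in delta RER, reported with its 95% CI. SALINE+PLAC minus LIPID+PLAC is reported separately, as a check that lipid lowered metabolic flexibility. The three-condition omnibus test is not used to conclude on carnitine.*

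The same sentence should say whether the contrast is tested one- or two-sided, since Section 4.4 sizes the trial one-sided and Section 10 is silent; the choice is the 80% versus 68% above.

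The change is a short rewording, with no extra subjects, measurements or procedures. The only thing given up is the option of citing a significant omnibus result in support of carnitine.

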## SUMMARY

**Rationale:** Insulin resistant subjects and type 2 diabetic patients are characterized by a decreased metabolic flexibility: a reduced capability to switch from fat oxidation in the basal state to carbohydrate oxidation in the insulin-stimulated state. This metabolic inflexibility is an early hallmark in the development of diabetes. Recent evidence suggests that a low carnitine availability may limit acetylcarnitine formation, thereby reducing metabolic flexibility. Thus, when substrate flux in the muscle is high, acetyl-CoA concentrations increase, leading to inhibition of pyruvate dehydrogenase (PDH) and thereby reducing glucose oxidation. The conversion of acetyl-CoA to acetylcarnitine relieves this acetyl-CoA pressure on PDH. To provide more direct insight into the effect of carnitine in preventing metabolic inflexibility and insulin resistance and to further explore the mechanism of action is the focus of this research. Here, we hypothesize that the capacity to form acetylcarnitine may rescue lipid-induced insulin resistance. To this end, insulin resistance will be induced by lipid infusion in healthy volunteers and it will be tested whether carnitine co-infusion can alleviate insulin resistance.

**Objective:** The primary objectives are to investigate whether L-carnitine infusion may rescue lipid-induced insulin resistance and whether L-carnitine infusion is improving metabolic flexibility in the state of lipid-induced insulin resistance. Furthermore, a secondary objective is to examine the molecular pathways of carnitine and acetylcarnitine, responsible for muscle insulin sensitivity.

**Study design:** The current study is an interventional randomized crossover trial in which each subject serves as its own control. Subjects will be blinded for the intervention.

**Study population:** n=13, healthy young (18-40 years) male subjects will be included.

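### Metabolic flexibility, a primary objective, is assigned an ordinary one-way ANOVA although every subject contributes all three conditions; with positive within-subject correlation the test is conservative and loses power.

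*Protocol*

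**What the plan says.** Metabolic flexibility has primary status in two places. Section 2 lists under the primary objective "To investigate whether L-carnitine infusion is improving metabolic flexibility in the state of lipid-induced insulin resistance". Section 8.1.1 lists among the main study parameters "Metabolic flexibility (delta RER between basal and insulin stimulated state".

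The design is within-subject throughout. The Summary states "The current study is an interventional randomized crossover trial in which each subject serves as its own control", and section 5.1, having put every subject through all three arms, concludes "Thus, each subject will act as its own control".

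Section 10.1 then gives two analyses in one paragraph. For insulin sensitivity, with condition and time as factors, "a two-way ANOVA for repeated measures is used". For metabolic flexibility, the comparison "will be determined by comparing metabolic flexibility between the conditions with a one-way ANOVA". Section 10.2 returns to the same three arms for the muscle parameters, which "will be analyzed with a one way ANOVA for repeated measured with post-hoc analysis if data allow to do so"; the plasma metabolites there also get a repeated-measures ANOVA. Among the between-arm tests, only the one for metabolic flexibility lacks the repeated-measures qualifier, and nothing elsewhere in the protocol supplies it.

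**The concern.** An ordinary one-way ANOVA treats the three sets of delta RER values as three independent groups. With 13 completers it has 39 values and 36 error degrees of freedom, and its error term contains the stable differences between subjects. A crossover is run to remove those differences. If they are substantial, the test uses a standard error that is too wide for the condition differences, and a real carnitine effect on the second primary objective can be missed.

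There is little slack. The sample size was set on insulin sensitivity with a within-subject SD, and metabolic flexibility has no calculation of its own. It relies on the same 13 subjects.

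**Working it through.** **1. The plan's own figure.** Inputs from section 4.4: effect 0.5 mg/kg/min, SD of the individual improvement 0.68 mg/kg/min, one-sided alpha 0.05, power 80%, N = 13. A paired t-test has n - 1 degrees of freedom and noncentrality (0.5/0.68) x sqrt(n). At n = 13 this is 0.735 x 3.606 = 2.65, and the power is 80.3%; at n = 12 it is 77.1%. N = 13 is therefore reproduced, as a paired calculation.

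**2. The standard error.** Let each delta RER have variance s², with correlation rho between any two conditions in the same subject.
- True standard error of a difference between two condition means: sqrt(2s²(1 - rho)/n).
- Standard error used by an ordinary one-way ANOVA: about sqrt(2s²/n).
- Ratio: 1/sqrt(1 - rho). This is 1.00, 1.12, 1.20, 1.41 and 1.83 at rho 0, 0.2, 0.3, 0.5 and 0.7.

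**3. Level and power by simulation.** The protocol gives no rho, SD or effect for delta RER, so these are assumptions:
- n = 13, three conditions, equal correlation between conditions;
- a standardised paired effect of 0.5/0.68, borrowed from the glucose-utilisation figures in section 4.4;
- LIPID+PLAC lower than the other two conditions, which are equal.

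The ordinary analysis uses F on 2 and 36 degrees of freedom. The repeated-measures analysis uses F on 2 and 24. The contrast is LIPID+CAR minus LIPID+PLAC, with the error term of the respective analysis.

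| rho | Actual level of the ordinary 5% F-test | Contrast power, two-sided 5%: ordinary | Contrast power, one-sided 5%: ordinary | F-test power: ordinary |
|---|---|---|---|---|
| 0 | 5.0% | 73% | 83% | 75% |
| 0.2 | 2.6% | 65% | 78% | 65% |
| 0.3 | 1.7% | 59% | 74% | 58% |
| 0.5 | 0.5% | 43% | 61% | 38% |
| 0.7 | 0.07% | 19.5% | 37% | 13% |

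The repeated-measures analysis holds its 5% level at every rho. Its power does not depend on rho, because the effect is scaled to the SD of the paired difference: about 72% for the two-sided contrast, 82% for the one-sided contrast and 73% for the F-test. The 82% exceeds the 80.3% of step 1 because the pooled error has 24 degrees of freedom instead of 12.

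**4. Reading the table.** For the two-sided contrast the loss is nil at rho 0, about 7 points at 0.2 (72 - 65), 13 at 0.3, 29 at 0.5 and about 52 at 0.7. One-sided, the side used in section 4.4, it is about 4, 8, 21 and 45 points at rho 0.2, 0.3, 0.5 and 0.7.

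**The case against.** The best defence is that the phrase is shorthand. The sentence closes a paragraph whose only other test is a repeated-measures ANOVA with condition and time; delta RER has no time factor, so one-way may simply mean the same analysis with time dropped. The opening of section 10 also removes a subject with a missing value from the analysis of that parameter, a rule that suits a within-subject analysis and is not needed for independent groups. The protocol never calls the values independent or unpaired. All of this is fair, and it means no deliberate choice of an unpaired test should be read into the text. But section 10.2 writes out the repeated-measures form of a one-way ANOVA for the same three arms, so the omission here is not the document's usual style. Someone running the named test in SPSS would run the wrong procedure.

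Second, the size of the loss is not fixed by the document. Delta RER is a change score, part of the stable between-subject variation cancels in it, and rho could be modest. This stands. A reader might infer that a large power loss, or a probable false negative, is established; the documents do not support that without a value of rho.

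Third, a reader might infer that the error invalidates a positive result. It does not: with positive rho the actual level is below 5%. Nor does it touch the means with SD or SEM that section 10 reports for each parameter; only the standard error of the differences between conditions is affected. Insulin sensitivity, on which the sample size rests, has a repeated-measures test.

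**Conclusion.** The test named for metabolic flexibility is wrong as written for this crossover. It is a stated method on a primary objective, not a detail left to a statistical analysis plan. The direction is certain for any positive rho: standard errors of condition differences too wide, a conservative test, and lost power. The amount is conditional. It runs from nothing at rho 0, through about 7 points of two-sided contrast power at rho 0.2, to about 29 points at rho 0.5 and more beyond. Those figures assume 13 completers, equal correlations and a standardised effect borrowed from another variable. The correction does not depend on them, since the ordinary ANOVA gains at most about one point for the contrast and two for the F-test at rho 0 and loses at the positive values examined.

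**What to change.** In section 10.1, replace the test for metabolic flexibility with a one-way ANOVA for repeated measures, with condition as the within-subject factor and subject as the block, matching section 10.2. State that the LIPID+CAR minus LIPID+PLAC contrast will be reported, and whether it is tested one- or two-sided. That is sufficient.

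A mixed model for delta RER with condition and visit fixed and subject random would serve equally well. Its visit term costs two error degrees of freedom with complete data (24 - 2 = 22). It can also keep a subject who lacks one condition, so the missing-value rule at the start of section 10 would have to be reworded to agree.

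The cost is one sentence, settled before the data are analysed. No subjects, visits or measurements are added.
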